**Methods:**

The AKETS is a 24–month, community–based, randomized controlled trial embedded in the prospective Aging Kidney Study cohort, which started in November 2018. A total of 141 participants aged 40–90 years are enrolled and allocated to one of the following three groups: (1) exercise intervention, (2) stretching intervention (active control), and (3) usual lifestyle (time control). The exercise program comprises individualized multicomponent training, including aerobic, resistance, and balance exercises, performed three times per week over 12 months.

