### Randomization and blinding

Participants are to be classified into one of the following three groups: (1) exercise intervention group, (2) stretching intervention (active control) group, and (3) usual lifestyle (time control) group (Fig. 2). Participants voluntarily choose to enroll in either the usual lifestyle group or one of two intervention groups (exercise or stretching). Assignment to the usual lifestyle or intervention group is determined based on participant preference and collected via a questionnaire administered after obtaining written informed consent. Only those who opt for the intervention arm are subsequently randomized into one of the two groups (i.e., exercise or stretching group). Randomization within the intervention arm is stratified by age, sex, and GFR stage and performed using a computer–generated randomization sequence following the completion of baseline assessments. The allocation ratio between the two intervention groups is 1:1. The random allocation sequence was generated by a study statistician (MG). Allocation of participants was conducted by an independent study investigator (YN) who had no direct contact with participants. Personnel involved in participant enrollment (KK) did not have access to the random allocation sequence at any stage, ensuring adequate allocation concealment. The investigators responsible for evaluating the primary outcome are independent of the study team and remain blinded to group allocation throughout the study period. However, due to the inherent characteristics of the interventions (structured exercise training versus stretching) and the need to describe the intervention procedures in the informed consent documents and study protocol, blinding participants to group allocation was not feasible. To mitigate the risk of performance bias, we standardized the frequency, duration, and monitoring procedures of both intervention programs.

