#### Usual lifestyle group (Time control group)

Within the AKS cohort, a group of participants who are followed up without receiving any intervention is designated as the usual lifestyle (i.e., time control) group for this study. The participants who opt for the time control group are instructed to maintain their usual lifestyle habits and encouraged to participate in annual follow–up assessments.

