### Statistical analysis

All analyses will be conducted based on the intention–to–treat (ITT) principle. Statistical significance is set at *P* < 0.05. Data are expressed as mean ± standard deviations, median [interquartile range], or frequency counts (%), as appreciate. Baseline group characteristics will be compared using one–way analysis of variance or the Kruskal–Wallis test for continuous variables and the chi–square test or Fisher’s exact test for categorical variables. The eGFR slope for the 6–year pre–intervention, 1–year during–intervention, and 1–year post–intervention phases will be calculated. For calculating the eGFR slope, the repeated measurements of eGFR will be analyzed using a linear mixed model (LMM) including continuous time as a fixed effect and individual participant as a random effect (henceforth, Model 1). In addition, the slope will be estimated using a single linear regression of eGFR on time by each participant (called as Model 2) as a supplementary analysis.

For a primary analysis, the eGFR slope will be compared using the LMM including the group (exercise, stretching, and usual lifestyle), time, their interaction term, and the baseline eGFR as fixed effects and individual participant as a random effect. The eGFR slopes calculated by Models 1 and 2 will also be compared between groups using analysis of covariance, including the group as a factor and the eGFR slope of the 6–year pre–intervention phase as a covariate. The eGFR slope for the 6–year pre–intervention, 1–year during–intervention, and 1–year post–intervention phases will be performed using paired t–tests for within–group comparison.

Secondary outcomes will be analyzed using the generalized estimating equations (GEE) method, including group, categorical time point (baseline, 6 months, and 1 year), and their interaction term as factors. In each model, an unstructured (UN) correlation matrix will be used to account for within–individual correlations across time points. If the UN matrix leads to a convergence problem for numerical optimization, a simpler correlation structure will be used. The results of the GEE analysis will be presented as the marginal means with 95% confidence intervals. Pearson product–moment correlation analysis and repeated–measure correlation analysis [50] will be conducted to examine the associations between individual changes in each outcome.

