This study has several limitations that should be considered when interpreting our findings. First, due to the voluntary selection of participants into either the intervention or usual lifestyle groups before randomization, there may be potential selection bias; participants opting into intervention groups could systematically differ in baseline health status compared to those choosing the usual lifestyle group. However, as shown in Table 1, the baseline characteristics of exercise, stretching, and usual lifestyle groups were generally comparable, with no substantial differences observed among the three groups. The second concern is the risk of participant dropout. The previous study has shown a completion rate of 80% [49], but this may be optimistic. The extent of dropout could affect the generalizability of the results. To address this concern, we plan to conduct sensitivity analyses to examine the robustness of our findings. Third, the risk of type I error is increased due to the presence of multiple secondary endpoints because the multiplicity of test for the endpoints will not be controlled. Therefore, results from the secondary analyses will be interpreted cautiously and viewed primarily as hypothesis–generating rather than confirmatory. Fourth, in participants with early diabetes or pre–diabetes, transient glomerular hyperfiltration could temporarily elevate eGFR, thereby masking initial declines in kidney function. To mitigate this issue, subgroup analyses stratified by baseline glycemic control status using hemoglobin A1c thresholds (e.g., ≥ 6.5%) will be conducted. Finally, it is important to note that our participants have relatively preserved kidney function compared to populations studied in previous CKD trial [49]; hence, the magnitude of exercise–induced benefits observed in prior CKD–specific studies might not directly generalize to our study population.

In summary, this study is the first long–term RCT in the field of sports nephrology to employ the TwiCs study design. In the context of an ultra–aged society in which the prevalence of CKD is expected to continue to rise, our study provides crucial clinical and physiological insights into the role of regularly performed exercise as a primary prevention for CKD in middle–aged and older adults.

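### The primary eGFR-slope model combines a preference-chosen group with the two randomised arms and names no primary contrast, so a non-randomised difference could be reported as the trial's main result

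*Protocol article*

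**What the plan says.** All places are in the protocol article.

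- **Randomization and blinding.** "Assignment to the usual lifestyle or intervention group is determined based on participant preference". Then: "Only those who opt for the intervention arm are subsequently randomized into one of the two groups". The ratio is given for those two groups alone: "The allocation ratio between the two intervention groups is 1:1".
- **Study design, procedure, and ethics, and Fig. 1.** The trial is described as a two-arm RCT.
- **Sample size calculation.** One two-sample t-test: difference 5 mL/min/1.73 m² per year, SD 8, two-sided 0.05, power 0.80, 84 in total.
- **Statistical analysis.** For the primary analysis, "the eGFR slope will be compared using the LMM including the group (exercise, stretching, and usual lifestyle), time, their interaction term", with baseline eGFR as a further fixed effect and participant as a random effect. A supporting ANCOVA compares the estimated slopes between groups with the pre-intervention slope as covariate. Neither analysis names a contrast, an order of testing or a division of alpha.
- **Introduction, hypothesis 1.** Its specific form compares the exercise group with its own earlier decline. It names no between-group contrast.
- **Discussion, limitations.** Self-selection is acknowledged, then answered by Table 1, "with no substantial differences observed among the three groups". The multiplicity caveat covers secondary endpoints only.
- **Abstract, Methods.** Participants in a randomised trial are "enrolled and allocated to one of the following three groups". That groups were partly chosen is not mentioned there.

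**The concern.** The design and sample size point to one randomised comparison, while the stated primary model has three groups, one formed by choice. A reader of the results cannot tell in advance which of these would count as the primary finding: exercise versus stretching, exercise versus usual lifestyle, or the overall group-by-time term. Only the first is protected by randomisation. People who opt for a year of structured activity may differ from those who decline in motivation, health behaviour and prior decline in kidney function. Any of these can affect later eGFR slope without an effect of exercise. The trial could therefore report a positive primary result when exercise did no better than its randomised control.

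**Working it through.** **1. The plan's own sample size.** Inputs from Sample size calculation: difference 5, SD 8, two-sided 0.05, power 0.80.

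- Normal approximation: n per arm = 2 × (1.960 + 0.842)² × 8² / 5² = 40.2, so 41 per arm and 82 in total.
- Exact t-test: 41.17, so 42 per arm and **84 in total**. The plan's figure is reproduced.

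This calculation covers one pair of groups. With the 43 and 45 randomised (Table 1), power under the same assumptions is 82.6% before dropout.

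**2. No true slope difference between any groups.** Group mean slopes were simulated with n = 43, 45 and 53, SD 8, pooled variance and 400,000 runs. This is a simplified stand-in for the mixed model. The two exercise contrasts share an arm, so their correlation is (1/43) / √[(1/43 + 1/45)(1/43 + 1/53)] = 0.53.

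| Rule at P<0.05 | Chance of a false positive |
|---|---|
| Exercise vs stretching only | 5% |
| Overall three-group test only | 5% |
| Either exercise contrast, ungated | 8.9% (independence would give 1 − 0.95² = 9.75%) |
| Any of three pairs, ungated | 12.1% (independence would give 1 − 0.95³ = 14.3%) |

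**3. Exercise equals stretching, but self-selection worsens the usual-lifestyle slope.** The documents give no size for such a shift. The range 1 to 3 mL/min/1.73 m² per year is an assumption.

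The standard error of exercise minus usual lifestyle is 8 × √(1/43 + 1/53) = 1.64. For a shift of 2 the standardised shift is 2 / 1.64 = 1.22, so the chance of significance is about P(Z > 1.96 − 1.22) = 0.23. The simulation gives:

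| Assumed shift | Overall test significant | Exercise vs usual lifestyle significant | Exercise vs stretching significant |
|---|---|---|---|
| 1 | 9% | 9% | 5% |
| 2 | 23% | 23% | 5% |
| 3 | 47% | 44% | 5% |

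The overall test keeps its 5% only when the shift is zero.

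**4. Does the model's adjustment remove this?** Baseline eGFR enters as a main effect. A term that does not vary with time changes a participant's level and leaves the group-by-time coefficients free to absorb any difference in rate of decline. It does not remove confounding of slope. The pre-intervention-slope covariate addresses this more directly, but it belongs to the supporting ANCOVA.

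**5. Does Table 1 settle it?** BMI is 21.2 in usual lifestyle against 22.6 and 22.4 in the two randomised arms. For exercise versus usual lifestyle the standardised difference is 1.4 / √[(4.1² + 2.9²)/2] = 0.39. This is modest, but both randomised arms differ from usual lifestyle in the same direction. Similar means on listed variables also say nothing about unlisted ones.

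**The case against.** The strongest reply is that a model is not a test. The exercise-minus-stretching slope is its own coefficient in the three-group model, and the third group mainly adds to the shared variance and baseline-eGFR estimates. The article states neither an overall test nor three pairwise tests, and the choice of contrast is often left to an analysis plan. The self-selection is disclosed in the methods and the limitations, and a pre-intervention-slope adjustment is already planned. Much of this stands: the randomised estimate is not spoiled, and nothing is concealed. What remains is that the article itself fixes a three-group primary model against a two-arm design and a two-group sample size. Disclosure does not say which comparison carries the claim.

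Several stronger readings are tempting but are not supported:

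- **That the plan has a 9% or 12% error rate.** Those figures need ungated pairwise reading, which the article does not state. With exactly three groups, pairwise tests made only after a significant overall test would keep 5% when no groups differ. That order is not stated either.
- **That fasting glucose in Table 1 shows self-selection.** Exercise versus usual lifestyle gives (84 − 91) / √[(14² + 16²)/2] = −0.47. The two randomised arms differ by (84 − 90) / √[(14² + 16²)/2] = −0.40, so the exercise arm is the outlier, after randomisation.
- **That the usual-lifestyle group has no 6-month data.** These participants are "encouraged to participate in annual follow–up assessments", but the assessment schedule lists a 6-month visit with no exception by group. The documents do not establish an empty cell.

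**Conclusion.** The point holds in this form: the stated primary analysis includes a preference-chosen group of 53 of 141 participants (38%) and names no primary contrast, which conflicts with the article's own two-arm design and two-group sample size. A non-randomised difference could therefore be reported as the primary result. The multiplicity caveat does not reach this, because it concerns secondary endpoints.

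The size depends on how the model is read. Ungated pairwise testing gives about 9% to 12% family-wise error when nothing differs. An assumed self-selection shift of 1 to 3 mL/min/1.73 m² per year makes the overall test significant in 9% to 47% of trials with no difference between exercise and stretching. Both results rest on the plan's SD of 8, equal variances and a slope-level approximation to the mixed model. The shift itself is not in the documents, and it is not shown that such bias exists here, only that the analysis as written would not separate it from an exercise effect.

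**What to change.** - In Statistical analysis, state one confirmatory between-group test: the exercise-minus-stretching difference in eGFR slope over 0–12 months, among the 88 randomised participants, two-sided 5%. This matches the existing sample size calculation.
- Report usual-lifestyle comparisons as non-randomised supporting analyses, using the pre-intervention-slope adjustment already planned.
- Treat the before-versus-during comparison within the exercise group (hypothesis 1) likewise as a non-randomised supporting analysis.
- In the limitations, do not use Table 1 similarity as grounds for treating the usual-lifestyle comparison as unbiased.
- In the abstract, describe two randomised arms plus one preference group.

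Make the change before outcome data are examined by group. It needs no new participants or measurements. The cost is that usual-lifestyle comparisons lose confirmatory status. Keeping both exercise contrasts as primary would be dearer: at Bonferroni 0.025 each, 50 per group would be needed and 43 versus 45 would give 74.1% power. That route would still leave one of the two contrasts non-randomised.

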### Primary and secondary outcome measures

The primary outcome of this study is the annualized rate of change in eGFR (i.e., eGFR slope), expressed as mL/min/1.73 m² per year. Based on findings from a recent meta–analysis of RCTs, the eGFR slope is recognized as a reliable surrogate endpoint for tracking CKD development [45, 46]. Given that serum cystatin C levels are less influenced by physical activity and muscle mass than serum creatinine levels [47], serum cystatin C levels are used to calculate the eGFR and evaluate changes in kidney function. The eGFR slope is determined using a linear mixed–effects model with random intercepts [48].

The secondary outcomes include alterations in renal hemodynamics and oxygenation assessed using Doppler ultrasound imaging and MRI, glomerular and tubular damage biomarkers, cardiovascular function indices, such as arterial stiffness and endothelial function, blood– and urine–based markers of mineral and bone metabolism, body composition and bone density, muscle strength, cardiorespiratory fitness, physical performance, habitual dietary intake, sedentary behavior, physical activity, sleep quality, and mental health. The detailed measurement methods for the secondary outcomes are provided in the Supplementary Material.

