A key difference between the handful of previous interventional studies examining the effects of exercise training on kidney health in individuals with or without CKD and our study is the fact that our study has the long–term observational data spanning six years before intervention initiation. This difference is important for addressing the clinical question of whether exercise can improve deteriorating kidney health, which has worsened over several years owing to aging and long–term lifestyle disruptions. To our knowledge, only one pilot study has been conducted with a similar design comparing changes in kidney function before and after the intervention, suggesting that exercise training can slow the progressive deterioration in kidney function in patients with CKD [49]. However, this pilot study had a small sample size (*n* = 20) and short pre–intervention follow–up period (one year) and did not conduct follow–up measurements after the intervention. Therefore, we aimed to address these limitations by adopting a better design (i.e., TwiCs) to clarify whether exercise improves, does not affect, or deteriorates kidney health.

Emerging evidence suggests that the deterioration in renal hemodynamics [12] and mineral metabolism [13] observed in early middle age may contribute to the rapid kidney function decline in later life. Based on these findings, preventive measures to minimize the deterioration of renal hemodynamics and mineral metabolism may lead to improved long–term renal outcomes. However, the long–term effects of preventive interventions on renal hemodynamics and mineral metabolism remain unclear. In this study, as a secondary outcome, we comprehensively investigated the effects of long–term structured exercise training on renal hemodynamics and mineral metabolism in middle–aged and older adults. This will allow us to provide new insights into the underlying mechanisms through which exercise training contributes to the suppression of kidney function decline.

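### The primary slope comparison adjusts only for the single baseline eGFR, and the companion ANCOVA uses the cohort history as a slope but not as a level, so precision already available for exercise versus stretching is left unused

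*Protocol article*

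**What the plan says.** All of this is in the protocol article.

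- **Primary model (Statistical analysis).** A linear mixed model in which the terms for study group and time are joined by "their interaction term, and the baseline eGFR as fixed effects"; the participant is the random effect. No eGFR value from before baseline is listed.
- **Companion analysis (same paragraph).** "The eGFR slopes calculated by Models 1 and 2 will also be compared between groups using analysis of covariance". The only adjustment named there is each participant's slope over the six years before the intervention.
- **Within-group use of the history (same paragraph).** The pre-, during- and post-intervention slopes are compared by paired t-tests.
- **Random effects (Primary and secondary outcome measures).** "The eGFR slope is determined using a linear mixed–effects model with random intercepts".
- **The value placed on the history (Discussion).** The contrast drawn with previous trials is that "our study has the long–term observational data spanning six years before intervention initiation".
- **Visits (Study design).** Baseline, 6, 12 and 24 months, with the intervention ending at 12 months.

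**The concern.** The design was chosen because the cohort supplies repeated eGFR values before randomisation, yet none of them enters the model named as primary. This matters because of how a 1-year slope is built. With visits at 0, 6 and 12 months, a straight-line slope per year has weights -1, 0 and +1, so about half of its measurement noise comes from the one baseline value. Earlier values say where the participant's level really was at randomisation and can remove part of that noise. A pre-intervention slope used alone carries little of that information.

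At stake is the precision of the only randomised contrast, exercise versus stretching. Enrolment is complete, and the Discussion itself doubts whether 80% completion will be reached.

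**Working it through.** **1. The plan's own figure.** Inputs from Sample size calculation: difference 5, SD 8, two-sided 0.05, power 0.80. The noncentral-t calculation gives 41.17 per arm, hence 42 per arm and 84 in total. This matches the article, and no covariate adjustment is involved. Table 1 shows 43 and 45 randomised.

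**2. What the baseline covariate does in the primary model.** If the baseline visit is among the responses, a balanced random-intercept model estimates group-by-time from within-person differences only. Baseline eGFR as a main effect is constant within a person and cancels. The variance of the contrast is then that of unadjusted slopes: 64 × (1/43 + 1/45) = 2.91. In simulation it was 2.92 both with and without the covariate (true slope SD 0.5).

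**3. Set-up for the gain.** Write y = a + b·t + e.

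- From the article: the SD of the 1-year slope d = y(1) - y(0) is 8, and the baseline SD is 19 (Table 1).
- Assumed, because not stated: true slope SD s from 0.5 to 1.5; 2 to 6 earlier values; within-person noise either independent or with correlation exp(-lag/T), T from 0.5 to 2 years.
- With independent noise, 64 = s² + 2v, so the noise variance v is 31.875, 31.5 and 30.875 for s = 0.5, 1 and 1.5.
- The share of variance removed by a covariate x is Cov(x, d)² / (Var(x) × 64).

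**4. Pre-intervention slope alone, six annual earlier values, independent noise.**

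*Baseline visit excluded* (times -6 to -1, sum of squares 17.5): Cov = s², Var = s² + v/17.5.
- s = 0.5: 0.25² / (2.07 × 64) = 0.05%
- s = 1: 1² / (2.80 × 64) = 0.6%
- s = 1.5: 2.25² / (4.01 × 64) = 2.0%

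*Baseline visit included* (times -6 to 0, sum of squares 28, weight on baseline 3/28): Cov = s² - 3v/28, Var = s² + v/28.
- s = 0.5: (-3.165)² / (1.388 × 64) = 11.3%
- s = 1: (-2.375)² / (2.125 × 64) = 4.1%
- s = 1.5: (-1.058)² / (3.353 × 64) = 0.5%

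With few earlier visits a slope that includes baseline does better. For values at -6, -3 and 0 years and s = 0.5, Cov = 0.25 - 31.875/6 = -5.06 and Var = 0.25 + 2 × 31.875/36 = 2.02, so the share is 25.6 / (2.02 × 64) = 20%.

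**5. Adding the level.** Take x = y(0) minus the mean of the six earlier values, with s = 0.5. Cov = 3.5 × 0.25 - 31.875 = -31.0. Var = 3.5² × 0.25 + (7/6) × 31.875 = 40.25. Share = 961 / (40.25 × 64) = 37%. With baseline, earlier mean and earlier slope all entered, the results are:

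| Setting (s = 0.5 to 1.5) | Variance removed |
|---|---|
| Six annual values, independent noise | 27 to 38% |
| Six annual values, all noise correlated, T = 1 year | 12 to 21% |
| Six annual values, all noise correlated, T = 2 years | 6 to 11% |
| Two earlier values, lowest result | about 6% |

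Adjusting for baseline eGFR alone in an ANCOVA of the slope removes 4 to 5%.

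**6. Power for a difference of 5** (noncentral t, SD = 8 × √(1 - share)). Completion of 80% leaves about 34 and 36.

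| Share removed | SD | 43 vs 45 | 34 vs 36 |
|---|---|---|---|
| 0 | 8.00 | 82.6% | 73.1% |
| 6% | 7.76 | 84.8% | 75.7% |
| 21% | 7.11 | 90.3% | 82.6% |
| 38% | 6.30 | 95.7% | 90.5% |

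Offsetting 20% dropout in full therefore needs a reduction of about 21%.

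**The case against.** A reader might infer that the plan ignores its six years of data. It does not: the ANCOVA with "the eGFR slope of the 6–year pre–intervention phase as a covariate" is prespecified, and so are the paired comparisons, which serve the article's first hypothesis of within-person change. What is missing is narrower: the history is absent from the primary model, and the earlier level is absent everywhere in the between-group analyses.

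It is also fair to say that the size of the gain cannot be read from the article. Under strong serial correlation it is small and would not make up for the expected dropout. If AKS visits were few and the pre-slope includes the baseline visit, the planned ANCOVA already captures a good part of the gain (step 4). The article also states no time window for the primary model, so the 0, 6 and 12 month layout is an inference from the assessment schedule.

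Finally, covariates chosen for precision are often left to an analysis plan, and nothing here makes a test invalid. That limits the weight of the point but does not remove it, because the article does fix the covariates of the primary model and of the ANCOVA.

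**Conclusion.** The point stands as one of efficiency. The primary model gains essentially nothing for the slope contrast from its baseline covariate, and the companion ANCOVA summarises the history in a way that usually recovers little. Adding baseline and earlier level lowered the variance in every setting tried. With slope SD 8, baseline SD 19, true slope SD 0.5 to 1.5 and 2 to 6 earlier values, the reduction is about 6 to 38%. The lower end belongs to strong serial correlation and the upper end to independent noise.

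Two stronger readings are not supported. The documents show no bias and no invalid test, and 88 were randomised against a requirement of 84 that assumes no adjustment. Nor do they secure full compensation for dropout, since that needs about a 21% reduction, which lies inside the range but is not assured.

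**What to change.** For the randomised exercise-versus-stretching contrast, extend the planned ANCOVA of the 1-year slope. Add baseline eGFR and the mean of the earlier AKS eGFR values next to the pre-intervention slope, and name this the primary between-arm estimate. Use the per-participant regression slopes (Model 2), because a model with random intercepts only yields no person-specific slope. Alternatively, enter the same covariates with time interactions in the primary mixed model. Keep the single-baseline model as a sensitivity analysis. State whether the pre-slope includes the baseline visit, and reconcile the length of the pre-intervention period, which is 5 years in the Introduction's hypothesis and 6 years in Statistical analysis and the Discussion.

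The cost is two more covariates, a rule for participants with few earlier values, and a gain that may turn out small. The data must be assembled anyway for the planned pre-intervention slopes. All added covariates predate randomisation, so they do not bias the randomised contrast.

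A single mixed model on all values with a knot at baseline is possible but should not be adopted with independent residuals. One simulation (1,500 runs per setting, not repeated, so only indicative) gave type I error of 3.7% under independent noise but 7.5% and about 10% at correlation times of 1 and 2 years. Such a model would need a serial-correlation structure or robust standard errors, and a person-specific change of slope after baseline.

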### Sample size calculation

The sample size calculation for this clinical trial is based on a previous study that explored the impact of a 1–year structured rehabilitation program on kidney function decline among patients with CKD, using a small sample from a TwiCs study design [49]. According to this previous study, the annual slope of eGFR (mL/min/1.73 m²/year) was approximately + 2 in the intervention group and − 3 in the control group, indicating a between–group difference of approximately 5 units per year. Assuming a standard deviation of 8, a two–sided significance level of 0.05, and a statistical power of 0.80, a total of 84 participants would be required based on a two–sample t–test.

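### The primary mixed model enters baseline eGFR only as a main effect and omits age and sex, so its slope comparison is not adjusted for the stratification factors

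*Protocol article*

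**What the plan says.** All references are to the Protocol article.

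- **Randomization and blinding.** "Randomization within the intervention arm is stratified by age, sex, and GFR stage". "The allocation ratio between the two intervention groups is 1:1". Entry to the usual lifestyle group is by the participant's own preference.
- **Primary and secondary outcome measures.** The primary outcome is the annualised eGFR slope. "The eGFR slope is determined using a linear mixed–effects model with random intercepts".
- **Statistical analysis, primary model.** "the eGFR slope will be compared using the LMM including the group (exercise, stretching, and usual lifestyle), time, their interaction term", followed by "and the baseline eGFR as fixed effects and individual participant as a random effect". Group by time is the only interaction named.
- **Statistical analysis, additional comparison.** Slopes are also compared between groups by analysis of covariance, "including the group as a factor and the eGFR slope of the 6–year pre–intervention phase as a covariate". This is not labelled primary, and no other covariate is listed.

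The terms of the primary model are written out in full, so the absence of age, sex and any covariate by time term is a stated choice and not a detail left to an analysis plan.

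**The concern.** Group by time carries the primary comparison. A covariate that acts only on a participant's level says nothing about how fast that participant's eGFR changes. A reader of the Statistical analysis section would take the primary slope result to be adjusted for baseline eGFR; in complete data it is not. Age and sex, which were important enough to stratify on, do not enter at all.

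Two things are at stake, and they differ by comparison. For exercise versus stretching, the question is precision and agreement between design and analysis. For either arm against usual lifestyle, randomisation gives no protection, and the one covariate in the model does not do the adjusting that its presence suggests.

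**Working it through.** **Inputs.** Slope difference 5, SD 8, two-sided alpha 0.05, power 0.80, total 84 (Sample size calculation). Visits at baseline, 6 and 12 months for the intervention year (Study design). Groups of 43, 45 and 53 (Table 1). Random intercept (Primary and secondary outcome measures).

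**1. The plan's own figure.** The article bases its calculation on earlier work "indicating a between–group difference of approximately 5 units per year". Normal approximation: n per arm = 2 × (1.96 + 0.8416)² × 8² / 5² = 2 × 7.849 × 2.56 = 40.2, so 41 per arm, 82 in all. The exact t-test solution is 41.17, so 42 per arm and 84 in all. The stated total reproduces. It uses no covariates.

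**2. Why the main effect cancels.** With a random intercept and complete visits at t = 0, 0.5 and 1 year, the slope information lies within participants. The mean time is 0.5 and Σ(t − 0.5)² = 0.25 + 0 + 0.25 = 0.5. Participant i's slope is

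b_i = [−0.5·y_i(0) + 0·y_i(0.5) + 0.5·y_i(1)] / 0.5 = y_i(1) − y_i(0).

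A main effect βx_i adds the same amount at each visit, so it contributes (−0.5 + 0 + 0.5)·βx_i / 0.5 = 0. Group by time remains the difference in mean b_i, whatever β is. The same holds for age and sex entered as main effects. A covariate by time term γx_i·t contributes γx_i to b_i, and so does adjust the slope.

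**3. Numerical check.** Random-intercept models were fitted to simulated trials of 43, 45 and 53 participants. The variances are assumptions; the cancellation does not depend on them. Entries are the exercise minus stretching slope difference.

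| Setting (one simulated trial each) | No covariate | Baseline main effect | Baseline × time |
|---|---|---|---|
| Complete visits | −3.6984 | −3.6984 | −3.1125 |
| Complete, 10-unit baseline imbalance imposed | −0.5696 | −0.5696 | −0.2835 |
| Complete, baseline left out of the response, same imbalance | 3.1161 | 3.1161 | 3.9626 |
| 20% dropout | −0.510 | −0.423 | −0.236 |
| 20% dropout, 10-unit imbalance imposed | −3.275 | −3.067 | −1.327 |

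In the complete-data rows, adding age and sex main effects also changed nothing. Over 40 complete-data trials without imposed imbalance, the largest change from any main effect was 0.0000. The largest change was 1.23 from baseline by time, and 1.69 from all three covariates by time.

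**4. Possible gain in precision.** If the covariates explain a share R² of slope variance, the SD becomes 8·√(1 − R²). The documents give no R², so these rows are assumptions.

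| R² | SD | Power, 42 per arm | Total N for 80% power |
|---|---|---|---|
| 0 | 8.00 | 0.808 | 84 |
| 0.05 | 7.80 | 0.827 | 80 |
| 0.10 | 7.59 | 0.847 | 76 |

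**5. Comparison with usual lifestyle.** In Table 1, mean eGFR is 81 against 85 and 86, a gap of 4 to 5 units; age is 69 against 68 and 67. If slope changed by an assumed 0.05 mL/min/1.73 m² per year for each unit of baseline eGFR, the unadjusted part would be 0.05 × 4 to 0.05 × 5, or 0.20 to 0.25 per year. The planned difference is 5. The figure scales with the assumed gradient, which the documents do not give.

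**The case against.** **The cancellation is not absolute.** The article expects dropout and calls an 80% completion rate possibly optimistic (Discussion, limitations). With incomplete visits the main effect does move the estimate. This stands as a limit on the claim. The movement comes from reweighting, however, and is not an adjustment of slopes for baseline eGFR.

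**The randomised comparison is protected.** Table 1 shows exercise and stretching close on the stratification factors: age 68 and 67, women 74% and 71%, eGFR 85 and 86. Leaving the strata out does not bias a randomised contrast. This stands in full. A reader might infer that the exercise versus stretching result is biased or left exposed to a chance imbalance; the documents do not support that.

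**The precision gain is not shown.** A reader might infer that the omission costs a definite number of participants. It does not follow, because R² could be zero. In one simulated trial, adding baseline by time lowered the standard error from 1.3110 to 1.3035, a variance gain of (1.3110/1.3035)² − 1 = 1.2%, or about one participant in 88. In the first row of the table above it rose, from 1.7614 to 1.7736.

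**Another planned analysis conditions on decline.** The ANCOVA uses each participant's pre-intervention slope, arguably a more direct driver than age or sex. This has weight for the plan as a whole. It is not the primary analysis, though, and it also leaves out age, sex and baseline eGFR.

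**Baseline may be both response and covariate.** A reader might see this as a further flaw. Where the term is inert for group by time, the double use does that contrast no harm. It becomes relevant only once baseline by time is added.

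**Conclusion.** The point holds as one of model specification. As written, the primary model's baseline term does not adjust the slope comparison, and two of the three stratification factors are absent. The cancellation is exact for complete common visits under the stated random intercept, and approximate once visits are missing.

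For exercise versus stretching, the consequence is an analysis that does not reflect the stratified design and a possible loss of precision of unknown size. The power range in the working depends entirely on the assumed R². For comparisons with usual lifestyle, slope differences tied to age, sex or baseline eGFR remain in the primary estimate; the gaps in Table 1 are modest, so the effect may be small, but its size cannot be derived from the article. Nothing here makes the sample size wrong. The change is worth making because the covariates are already collected.

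**What to change.** Before outcome data are analysed, amend the primary model in one of two ways.

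1. Add age by time, sex by time and a baseline kidney-function term (baseline eGFR or GFR stage) by time, each with its main effect. Main effects alone would not do. State whether the baseline value stays in the response. GFR stage is presumably a coarsened form of the same measurement, so it reduces the double use without removing it.
2. Alternatively, keep baseline in the response with a common baseline mean for the two randomised arms only, and add age by time and sex by time with their main effects. The constraint should not extend to the usual lifestyle group, which was not randomised.

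In the slope ANCOVA, add age, sex and baseline eGFR alongside the pre-intervention slope.

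The cost is a sentence or two of model wording and a few degrees of freedom. No new data and no change to the sample size are needed.
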